## 2. Methodology

### 2.1. Trial Design

This is a single-centre double-blind study of the effects of mixed air pollutants on the cognitive function of healthy human volunteers with a family history of increased risk of dementia. Participants will all undertake sequential controlled exposures to four air pollutants and clean air as control exposure, i.e., a repeated measures design. Cognitive testing, biological sampling, and physiological tests will be carried out before and after each exposure. The study design is outlined in Figure 1.

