### 2.7. Data Analysis

Data generated by this study will be analysed using longitudinal statistical modelling designed to account for the repeat measures in individual subjects (e.g., general estimating equation or random effects modelling, depending on the extent and nature of any missing or partial data). This will describe and account for changes in pre-exposure measures over time, comparing the effects of the different air pollution exposures to the clean air control.

Cognitive subscales will be entered into this process separately, to aid in pairing aerosols with undesirable changes identified in each cognitive domain. Our goal is to ensure an equal representation of biologically male and female participants, acknowledging potential sex-dependent effects of exposure. Consequently, biological sex will be entered as a covariate of interest during analysis.

In addition to ranking cognitive impacts in relation to the exposure sources, these data will be related to biomarkers of systemic and neuro-inflammation/injury to test the secondary hypothesis that acute cognitive effects and more severe downstream neurological impacts reflect underlying inflammatory processes.

Specifically, our primary and secondary end points are as follows:

Primary end point:

Evidence of impairment in cognitive function post exposure as measured by any of these cognitive tasks compared to clean air:Difference in the Approach bias measured via the Expression Recognition Task post pollutant exposure;Change in the Cognitive Control response time post pollutant exposure;Change in the 2-back discrimination index post pollutant exposure.

Secondary end point:

Change in performance on any of these cognitive tasks post pollutant exposure compared to clean air:Psychomotor Vigilance Task;Purdue Pegboard Test;Evidence of inflammatory or immune signals post exposure to pollutants compared to clean air;Change in lung function post pollutant exposure compared to clean air;Change in DNA post pollutant exposure compared to clean air.

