We believe that, despite the increased risk of errors, the study is worthwhile with this smaller sample size, especially considering the feasibility of recruiting clinically healthy participants over the age of 50 with a family history of dementia. Furthermore, the identification of statistically significant results, showing that different pollution exposures result in different cognitive endpoints, has the potential to inform and refine policy. Indeed, hazard ranking of common air pollutants for the emerging health risk of dementia will be compelling to government, policymakers, and regulators, as well as the medical community and the public, facilitated by public health agencies and other key stakeholders.

This study aims to demonstrate that our methodology can discriminate between the cognitive impairment effects of several major representative sources of air pollution. Future research will be able to build on the results of this study by introducing further parameter space, including but not limited to air pollution co-exposures and pollutants aged under atmospheric irradiation, and targeting wider participant groups. The initial outcomes from the study resulting from this protocol will allow future work to focus on the areas of cognitive dysfunction identified.

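### Separate pollutant-versus-clean-air tests for each cognitive subscale do not test whether pollutants act on different cognitive endpoints, which is the conclusion the Discussion draws from them

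*Protocol article*

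**What the plan says.** Section 2.1 sets out the design: "Participants will all undertake sequential controlled exposures to four air pollutants and clean air as control exposure, i.e., a repeated measures design". Section 2.7 proposes longitudinal models (estimating equations or random effects) for "comparing the effects of the different air pollution exposures to the clean air control". It then says how the cognitive results will be used: "Cognitive subscales will be entered into this process separately, to aid in pairing aerosols with undesirable changes identified in each cognitive domain". The primary end point covers three cognitive measures and is met by any of them: "Evidence of impairment in cognitive function post exposure as measured by any of these cognitive tasks compared to clean air".

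Section 3 (Discussion) gives the reading of the results: "the identification of statistically significant results, showing that different pollution exposures result in different cognitive endpoints, has the potential to inform and refine policy". It adds that the study aims to demonstrate that "our methodology can discriminate between the cognitive impairment effects of several major representative sources of air pollution", and that "The initial outcomes from the study resulting from this protocol will allow future work to focus on the areas of cognitive dysfunction identified".

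**The concern.** The Discussion's claim concerns a difference between pollutants in which endpoints they affect. Its null hypothesis is that the pollutants share the same effects across the outcomes. The comparison named in section 2.7 has another null: within one subscale, a given pollutant equals clean air. Rejecting that for pollutant A and failing to reject it for pollutant B leaves open whether A and B differ. Models fitted separately by subscale also contain no term that compares domains.

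With four pollutants and three primary measures there are 4 × 3 = 12 such tests on a small sample. At moderate power, chance alone decides which of the 12 cross the threshold, and the resulting pattern can look like a source-specific cognitive profile. The Discussion ties such results to refining policy and to directing future work towards the domains identified, so a chance pattern could be taken for a property of the sources.

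**Working it through.** **1. The plan's own figures (section 2.3.1).**
- Original sample size: ((1.960 + 1.282) × 25/15)² = 29.2, so 30. This reproduces.
- Revised sample size: a repeated-measures F test with λ = f² × n × m/(1 − ρ), f = 0.45, ρ = 0.5 and m = 4 measurements. At n = 11, λ = 0.2025 × 11 × 4/0.5 = 17.82 and power is 92.8%. At n = 10, λ = 16.2 and power is 89.6%. So 11 reproduces if 0.45 is Cohen's f over four measurements. A paired comparison with d = 0.45 would need 54.
- Either way the calculation concerns one outcome. It does not address differences between domains.

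**2. Sample size for the check.** The Discussion's target is 15 with 33% dropout: 15 × 0.67 = 10.05, about 10 completers. I used n = 10, and n = 15 as the best case.

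**3. Assumptions not given in the article.** Correlation of 0.3 between the three primary outcomes; one shared clean-air session; paired t tests at two-sided 0.05, counted when significant in the harmful direction; d = mean pollutant-minus-clean-air difference divided by its within-person SD. All four pollutants have the same d on all three outcomes, so the claim that they differ is false by construction.

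**4. Result.** Percentage of simulated trials (20,000 per setting) in which at least two pollutants have different, non-empty sets of significant outcomes:

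| d | n = 10 | n = 15 |
|---|---|---|
| 0 | 2 | 2 |
| 0.45 | 49 | 68 |
| 0.5 | 57 | 75 |
| 0.6 | 72 | 85 |
| 0.8 | 86 | 72 |
| 1.125 | 60 | 16 |

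Repeat runs differ by about one percentage point, hence the ranges 48-87% (n = 10) and 67-85% (n = 15) for d from 0.45 to 0.8.

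**5. Where d of about 1.1 comes from.** Suppose 0.45 is Cohen's f over five conditions, with four equal pollutants and clean air at zero. The SD of the condition means is δ × √(0.8 × 0.2) = 0.4δ, so δ = 0.45/0.4 = 1.125 SDs. With correlation 0.5, the SD of a difference is √(2 × (1 − 0.5)) = 1 SD, so d = 1.125.

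**6. Direct tests on the same data.** A pollutant-by-outcome interaction F test (6 and 6(n − 1) df) rejects in about 5% of trials in every setting. So does a between-pollutant F test within a single outcome.

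**7. Power of one pollutant-versus-clean-air test.** The miss rate at n = 10 is 75% (d = 0.45), 71% (0.5) and 38% (0.8). At n = 15 it is 63%, 56% and 18%.

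**8. Multiplicity adjustment is no cure.** Here the count is looser: the four profiles are not all identical, with an empty profile counted as a profile. At n = 10, Bonferroni over 12 tests still gives 32% (d = 0.45), 53% (0.6) and 93% (1.0).

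**The case against.** The strongest reply is that the plan never states the faulty rule. Section 2.7 speaks of changes being identified and sets no p-value criterion. The significance reading comes from one sentence in the Discussion, which could be taken to mean a significant between-exposure difference. Section 2.3.1 describes comparing the four exposures, and a subscale model with a five-level exposure factor can supply pollutant-versus-pollutant contrasts. An analysis plan that is not shown may specify them. Domain specificity is not a stated objective either: section 1.2 asks for a ranking.

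Part of this stands. A reader might infer that the plan sets an explicit rule of pairing by significance; it does not. A reader might infer that missed domains will be declared unaffected; no text says so, and the Discussion warns of Type II error and random fluctuation. A reader might also infer that a source-to-domain map is what the article calls compelling to policymakers; that phrase is attached to hazard ranking, and the sentence on differing endpoints claims only potential.

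What does not fall away is the pairing of a stated analysis with a stated conclusion. The comparator named in section 2.7 is clean air, the subscales are kept apart, the stated use is pairing, and the Discussion says what significant results would show. An analysis plan could add a suitable test, but the published inference would still need rewording.

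A further objection is that a cross-domain test on standardised, unlike measures (approach bias, response time, discrimination index) depends on how reliable each task is. That is fair. It is a reason to put direct contrasts within each subscale first and to be sparing with claims of domain specificity.

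**Conclusion.** The point holds as a mismatch between the comparison described and the conclusion drawn from it. Pollutant-versus-clean-air tests, subscale by subscale, cannot show that exposures result in different cognitive endpoints.

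The size depends on assumptions the article does not supply. For d between 0.45 and 0.8, identical pollutants would appear to have different profiles in about half to seven-eighths of trials with 10 completers, and in about two-thirds to 85% with 15.

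Two stronger statements are tempting and fail. Identical pollutants would not always, or even usually, look different: the rate is about 2% if no exposure has an effect and 16% at d of about 1.1 with all 15 completing (59% with 10). Nor does each test miss most real effects: at d = 0.8 it misses 38% (n = 10) or 18% (n = 15). The reasoning error is the same at every effect size; only how often it misleads varies.

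**What to change.** In section 2.7:
- Base any statement that sources differ on pollutant-versus-pollutant contrasts, with confidence intervals, from each subscale's repeated-measures model.
- Claim domain specificity only if a pollutant-by-domain test on standardised outcomes, all signed so that higher is worse, supports it.
- Otherwise present the source-by-domain map as descriptive estimates with intervals, and state that a non-significant cell is not evidence that a domain is unaffected.

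In the Discussion, reword the sentence on significant results so that a mix of significant and non-significant comparisons with clean air is not said to show different endpoints.

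The cost is wording plus contrasts and one additional model on data already being collected. The downside is low power. A single pairwise contrast with a true standardised difference of 0.45 would be detected in about 25% of trials with 10 completers and 37% with 15. The trial will therefore often have to report that differences between sources or domains were not shown.

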### 1.2. Objectives

The primary objective of this study is to rank the acute effects of a range of air pollution exposures on cognitive function in healthy aged individuals with a family history of increased dementia risk.

The secondary objective of this study is to identify evidence of changes in inflammatory or immune signals post exposure to pollutants compared to clean air, exploring possible underlying mechanisms of any identified cognitive changes.

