#### 2.3.1. Power Calculation

Based on effect size and variance from a currently unpublished study [35] looking at cognitive load and attention (measured as change in response time (
Δ
RT) after Diesel Exhaust exposure (
Δ
RT = 22 ms, s.d. = 25 ms), a sample size of 30 subjects will have 90% power to detect significant response time changes of 15 ms assuming the standard significance level of *p* < 0.05. We acknowledge this current study is a different design utilising an older adult population and have, therefore, calculated for a slightly smaller effect size than that of the previous study to compensate for larger RT variance in older adults. As longitudinal studies are prone to extensive participant attrition, the sample size of 45 aims to allow full data to be collected for a minimum of 30 participants. Power calculations were performed using PS [36].

In response to recruitment challenges, we revised the sample size, prompting a re-exploration of the sample size estimate and power calculation to identify the minimum sample likely to yield valuable results. The proposed study design involves comparing the impact of four pollution exposures by examining the differences between pre- and post-exposure measurements relative to baseline measurements. The independent design from the previous study, featuring one measure per group, makes it unfeasible to extrapolate data. Therefore, under the assumption of a conservative correlation among repeated measures set at 0.5, a minimum sample size of 11 participants is needed to achieve 90% power in detecting a moderate (0.45) effect size at a significance level of 0.05.

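### The any-of-three primary endpoint allows 12 chances to claim impairment with no error control stated, and the stated contrasts with clean air do not address the ranking objective

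*Protocol article*

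**What the plan says.** Section 2.7 (Data Analysis) gives the primary endpoint as "Evidence of impairment in cognitive function post exposure as measured by any of these cognitive tasks compared to clean air". Three outcomes follow: "Difference in the Approach bias measured via the Expression Recognition Task post pollutant exposure"; "Change in the Cognitive Control response time post pollutant exposure"; and "Change in the 2-back discrimination index post pollutant exposure". The same section enters the cognitive subscales into separate models and compares each pollutant with the clean-air control.

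Section 2.1 (Trial Design) supplies the exposures: "Participants will all undertake sequential controlled exposures to four air pollutants and clean air as control exposure, i.e., a repeated measures design".

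A significance level appears only in section 2.3.1 (Power Calculation). The first sizing is made "assuming the standard significance level of" 0.05, and the revised sizing again uses 0.05. Neither divides it across outcomes or pollutants.

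Section 1.2 (Objectives) states: "The primary objective of this study is to rank the acute effects of a range of air pollution exposures on cognitive function". Section 2.7 mentions ranking by source but gives no pollutant-versus-pollutant contrast and no rule for ordering. The Discussion (section 3) builds on both: "the identification of statistically significant results, showing that different pollution exposures result in different cognitive endpoints, has the potential to inform and refine policy".

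**The concern.** The endpoint is disjunctive: one favourable contrast among several is enough. Such a rule holds its error at 5% only if something is done about the number of chances, and the article pairs it with a single 0.05. At stake is a claim that a common pollutant acutely impairs cognition, which could arise from exposures with no effect far more often than a reader would assume from a 5% level.

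The second part is a mismatch of question and contrast. The objective is an order among four pollutants, but the stated comparisons are each with clean air. Setting a significant result for one pollutant beside a non-significant one for another invites the conclusion that the first is worse, which those tests do not examine.

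**Working it through.** **Inputs**
- Outcomes: 3, analysed separately (section 2.7).
- Pollutants: 4, with one shared clean-air control within each participant (section 2.1).
- Level: 0.05 (section 2.3.1). Sidedness is not stated; two-sided is assumed.
- Between-task correlation: not given; assumed, over the range 0 to 0.8.

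**1. The plan's own sizings.** The first, with 15 ms, SD 25 ms and 90% power, reproduces as a single paired contrast: ((1.960 + 1.282) × 25/15)² = 29.2, so 30 (88.8% power with the noncentral t). The revised figure reproduces as a repeated-measures F test over four levels with f = 0.45 and correlation 0.5: λ = 0.45² × 11 × 4 / (1 − 0.5) = 17.8, power 92.8% at n = 11 and 89.6% at n = 10, so a minimum of 11. Each sizing therefore fits one test of one outcome at 0.05.

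**2. Number of contrasts.** 3 outcomes × 4 pollutants = 12.

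**3. Correlation within an outcome.** Write s² for the within-participant variance of the change under each exposure, taken as equal. Two contrasts that share clean air have covariance s² and variance 2s² each, so their correlation is s²/2s² = 0.5.

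**4. Chance of at least one false claim when no exposure has an effect.** This comes from simulating 12 correlated normal statistics, each contrast tested at 0.05:

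| Between-task correlation (assumed) | Either direction, two-sided 0.05 | Harmful tail of two-sided 0.05 | Harmful direction, one-sided 0.05 |
|---|---|---|---|
| 0 | 40% | 22% | 37% |
| 0.3 | 38% | 20% | 34% |
| 0.5 | 36% | 18% | 31% |
| 0.7 | 31% | 16% | 27% |
| 0.8 | 29% | 14% | 25% |

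Simulating t tests with 10 or 15 participants gives nearly the same values (two-sided 39% at correlation 0, 28-29% at 0.8). One outcome alone, with its four contrasts, gives about 15%.

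The harmful-tail columns need a harmful direction for each outcome. The article lists approach bias only as a difference and gives none.

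**5. The ranking question.** Four pollutants form 4 × 3 / 2 = 6 pairs. Under the equal variances of step 3, a pollutant-versus-pollutant difference has the same standard error as a contrast with clean air. If one pollutant's statistic falls just above 1.96 and another's just below, the first is significant and the second is not, yet the statistic for their difference is close to zero. The contrasts with clean air therefore cannot stand in for the comparison that a ranking needs.

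**The case against.** The strongest reply is that the article is a summary. It leaves even the choice of model open and refers to a full protocol that is not shown; an analysis plan may also exist. Adjustment methods and contrast lists commonly sit in such documents. The 0.05 appears in the sizing, not as a decision rule for the 12 contrasts. That much stands: a reader might infer that the tests will be unadjusted at 0.05 each, but the article does not say so, and the figures above are conditional on that reading.

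The revised sizing also fits an omnibus test. If each outcome had to pass such a test first, the two-sided chance at n = 10 would be about 9-12%, or 5-6% counting harmful results only. No such gate is stated, however.

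A reader might also compute 1 − 0.95¹² = 46%. That requires 12 independent tests, which the shared clean-air control rules out; about 40% is the ceiling under the equal-variance model used here.

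On ranking, a reader might infer that the order will carry no uncertainty, or try to put a probability on a wrong order. Neither is supported. Section 2.7 plans ranking alongside a longitudinal model that yields standard errors, and the article gives no pattern of true effects from which to compute such a probability.

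What the reply does not remove is the rule itself. The any-of criterion is written as the primary endpoint and is not a detail left for later. The Discussion does acknowledge a raised risk of errors from the small sample, but the error it names is Type II; it does not address false positives from 12 contrasts.

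**Conclusion.** The point holds in this form: a disjunctive primary endpoint over 12 contrasts, sized at one undivided 0.05, with no error control stated in the article. Tested at 0.05 each, the chance of at least one false claim is about 29-40% two-sided, or about 14-22% if only the harmful tail counts. Even the lowest of these is nearly three times 5%. The size rests on four assumptions: no true effect of any exposure, equal variances, between-task correlation from 0 to 0.8, and testing of each contrast at 0.05.

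The mismatch between a ranking objective and contrasts stated only against clean air also holds. It is a matter of which comparison is made and needs no numerical assumption. It does not mean that ranking is absent from the plan: section 2.7 intends it, but does not say which comparisons would support it.

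**What to change.** Before unblinded analysis, replace the bare any-of rule with a procedure that holds the family of three outcomes by four pollutants at an overall 0.05. One option is Dunnett-adjusted contrasts with clean air within each outcome, at a level adjusted for multiplicity across the three outcomes; an equivalent valid procedure would serve. Claim impairment only for contrasts that pass. If an adjustment already exists in the full protocol or analysis plan, state it beside the endpoint. Section 4.5 expected analysis to start in January 2024, so if unblinded results have already been seen, date the change and say so.

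From the same model, report the six pollutant-versus-pollutant differences with confidence intervals and rank probabilities, and call pollutants ranked only where these support it.

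No new data are needed, but each single contrast then needs a larger effect. Bonferroni over 12 gives an upper bound on this cost: 0.05/12 = 0.00417, with a family-wise error of 3.3-4.5% under the correlations above.
- At n = 11, the effect detectable with 90% power rises from 1.09 to 1.59 SD of the paired difference.
- For 15 ms with SD 25 ms, power at 30 completers falls from 89% to 57%. Keeping 90% would take ((2.865 + 1.282) × 25/15)² = 47.8, so 48 completers (52 with the t distribution).

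Dunnett-type methods lose less than this because they use the correlation from the shared control.

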### 2.8. Data Management and Monitoring

The study will be subject to the audit and monitoring regime of the University of Manchester. All research staff involved in this study will be familiar with the protocol and suitably qualified, trained, and competent to carry out the required techniques. Staff are also trained in ICH-GCP, local information governance policies, and the data protection act. The source documents will be defined as the printed reports for any study measurement completed on a piece of equipment with this capability, or the case report forms designed by and completed by research staff. All research related documentation including the site file, case report forms, etc., will be kept with the PI until the results of the study have been analysed and published. Then it will be boxed and archived offsite for a minimum of 5 years. Archiving and destruction logs will be generated.

